## **6-2. Examination/Observation Items During Treatment Protocol and Observation Periods**

During this clinical trial, the following tests and observations are periodically performed and evaluated according to the safety evaluation schedule and the relapse evaluation schedule. For details of the timing of each inspection and observation, refer to “Examination items and evaluation schedule”. For hematology/blood biochemistry testing and adverse events, report the worst grade observed during each course in the “Treatment Course Report Form” (adverse event: clinical laboratory test value, subjective findings)”.

1) PS

2) Hematology tests

RBC count, hemoglobin, hematocrit, WBC count, WBC fraction, thrombocyte count

3) Blood biochemistry tests

Total serum bilirubin, AST, ALT, ALP, total plasma protein, serum creatinine

4) Tumor markers

CEA, CA19-9

5) Simple chest radiography or chest CT

6) Abdominal ultrasound, abdominal CT

7) Colonoscopy

If preoperative colonoscopy findings are inadequate, a contrast colon examination or colonoscopy is performed within 6 months postoperatively and the remaining colon is examined.

8) Adverse events

Registered cases are determined based on the Common Terminology Criteria for Adverse Events (CTCAE) V 3.0 adverse event criteria (Appendix 2 for filling out case record forms).

“Adverse event” refers to any undesirable or unintended signs (including anomalies in clinical laboratory values), symptoms or diseases that occur when a pharmaceutical is administered, and a causal relationship with the study drug; the presence or absence of the study drug does not matter.

Self-cognitive symptoms should be observed during the administration period and up to 28 days after the last administration and recorded according to the adverse event criteria of the CTCAE V 3.0. Based on the judgment of the attending physician, adverse events not described by this standard are evaluated on a grade scale: I: mild, II: moderate, III: more severe, IV: severe.

9) Drug adherence

Dose initiation date, daily dosage, medication days, missed or reduced doses for each course and reasons

Notwithstanding the above, other clinical examinations deemed clinically necessary are also conducted as appropriate.

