**5-4-2. Off-drug periods/dose reductions/therapy reinitiation provisions**

Adverse events are evaluated based on the Japanese-language Common Terminology Criteria for Adverse Events (CTCAE) v3.0 Japan Clinical Oncology Group/Japan Society of Clinical Oncology (JCOG/JSCO) version. Off-drug periods, dose reduction, and therapy reinitiation due to the occurrence of adverse events during capecitabine administration are managed according to “Table 3 Off-period/dose reduction criteria” and “Table 4 Reduced dosages”. In addition, handling of Grade II/III hand-foot syndrome, diarrhea, nausea, and vomiting shall be performed in accordance with “5-4-3. Provisions for off-drug periods/dose reductions/therapy reinitiation following adverse events not falling under the above”.

Clinical laboratory values may also be treated as adverse events in the following cases only:

(1) In case of a serious adverse event

(2) In cases where dose reduction, an off-period, or discontinuation of the protocol treatment is necessary

(3) When medical treatment is necessary

(4) When determined to be clinically problematic

1) Warnings concerning off-drug periods, dose reductions, and therapy reinitiation provision are as follows.

(1) Off-drug periods and dose reduction owing to worsening complications observed before the start of administration may be arranged based on fluctuations in adverse event grade, if deemed appropriate by the attending physician. For example, if Grade I alkaline phosphatase before administration deteriorates to Grade II during capecitabine administration, this may be treated as a Grade I adverse event, understood as a shift in adverse event grade.

(2) If the attending physician determines that adverse events do not cause interruption or delays in administration, such as in cases of alopecia or dysgeusia, and it is determined that there is no possibility of the event becoming serious, administration of capecitabine may be continued at the same dosage without an off-period or dose reduction.

(3) When anemia is controllable by transfusion, there is no need for an off-period or dose reduction, and treatment may continue at the same dose.

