| Grade 2 | 1st onset  2nd onset  3rd onset  4th onset | Off-drug until improvement to Grade 0-1  Off-drug until improvement to Grade 0-1  Off-drug until improvement to Grade 0-1  Suspend protocol treatment | Dose reduction not needed  Dose reduction 1  Dose reduction 2  － |
| Grade 3 | 1st onset  2nd onset  3rd onset | Off-drug until improvement to Grade 0-1  Off-drug until improvement to Grade 0-1  Suspend protocol treatment | Dose reduction 1  Dose reduction 2  － |
| Grade 4 |  | Suspend protocol treatment | － |

Note) Number of onsets refers to the number of appearances of events of the same grade, and is not limited to the number of appearances of the same event.

Table 4 Reduced dosages

| Body surface area | Single dose | | |
| --- | --- | --- | --- |
| Initial dose | Dose reduction 1 | Dose reduction 2 |
| ≤1.13 m2 | 1,500 mg (5 tablets) | 900 mg (3 tablets) | 600 mg (2 tablets) |
| ≥1.13 m2　≤1.21 m2 | 1,200 mg (4 tablets) |
| ≥1.21 m2　≤1.33 m2 | 900 mg (3 tablets) |
| ≥1.33 m2　≤1.45 m2 | 1,800 mg (6 tablets) |
| ≥1.45 m2　≤1.57 m2 | 1,500 mg (5 tablets) |
| ≥1.57 m2　≤1.69 m2 | 2,100 mg (7 tablets) |
| ≥1.69 m2　≤1.77 m2 | 1,200 mg (4 tablets) |
| ≥1.77 m2　≤1.81 m2 | 1,800 mg (6 tablets) |
| ≥1.81 m2 | 2,400 mg (8 tablets) |

**5-4-3. Provisions for off-drug periods/dose reductions/therapy reinitiation following adverse events not falling under the above**

1) Grade II/III hand and foot syndrome

Adverse event grade is determined based on the criteria in “Table 5 Diagnostic criteria for hand-foot syndrome” below and subject to “Table 3 Off-period/dose reduction criteria” above.

Table 5 Diagnostic criteria for hand-foot syndrome

| Grade | Clinical area | Functional area |
| --- | --- | --- |
| 1 | Numbness, skin hypersensitivity, burning, tingling, painless swelling, painless erythema | Everyday activities are not impaired |
| 2 | Swelling accompanying painful skin erythema | Everyday activities are somewhat impaired |
| 3 | Moist desquamation, ulcers, blisters, strong pain | Everyday activities are impossible |

If the grade of the corresponding symptom is inconsistent between the diagnostic areas (clinical area, functional area), adopt a grade that can be determined to be more suitable.

This criterion applies only to the diagnosis of hand-foot syndrome, and not to diagnoses of skin or other organ-related symptoms.

2) Grade II/III diarrhea, nausea, and emesis

Discontinue capecitabine use and take appropriate countermeasures.

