## **5-5. Treatment Discontinuation Provisions**

**5-5-1. Treatment discontinuation criteria**

If applicable, the attending physician will discontinue subsequent treatments and take appropriate measures. Investigators should observe and inspect for the evaluation items specified in “Table 6 Examination items and evaluation schedule” below at the time of discontinuation and record their findings and the accompanying rationale in their case report. In cases of termination, the attending physician shall promptly submit an administration progress survey to the study secretariat via fax.

1) When a subject him/herself withdraws consent

2) When a subject him/herself requests discontinuation of the protocol treatment

3) When recurrence of the original disease is observed

4) When novel cancerous lesions (duplicated cancer or multifocal colorectal cancer [excluding M cancer]) occurs

5) When the attending physician determines that protocol continuation will be difficult due to deterioration of comorbidities or onset of complications

6) When there is no relief or disappearance of symptoms following withdrawal due to an adverse event that falls under the off-period/dose reduction provisions (delay of treatment start by over 3 weeks or withdrawal)

7) If administration cannot be continued due to the occurrence of an adverse event even after 1 or 2 level reductions under the off-period/dose reduction provisions

8) If an adverse event of Grade IV occurs, the protocol treatment must be discontinued. (If capecitabine treatment is restarted at the discretion of the attending physician after protocol termination, a case report must be submitted.)

9) When the attending physician determines that protocol continuation will be difficult owing to an adverse event

10) If a subject dies

11) When the protocol treatment cannot be continued because the subject was transferred to a hospital

12) If a subject is determined to be ineligible after enrollment

13) Other cases in which the attending physician deems it necessary to terminate the protocol treatment

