**9-1-2. Unknown Grade 4 non-hematological toxicity**

“Unknown adverse events” are adverse events not described in a product’s package insert or prescribing information.

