**9-1-3. Life-threatening adverse events**

“Life-threatening adverse event” refers to known Grade IV hematological toxicities, known Grade 4 non-hematological toxicities, and fever/bleeding symptoms.

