## **9-2. Reporting Procedure**

In the event of an adverse event that is subject to emergency reporting requirements, the attending physician will promptly inform the study site supervisor. The study site supervisor will orally report to the study secretariat within 24 hours if adverse events subject to emergency reporting are observed. Furthermore, within 72 hours after adverse event discovery, the required items shall be recorded on an “Emergency Adverse Event Reporting Form” (APPENDIX 1: in-hospital reporting is also possible) and sent via fax to the study secretariat.

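### The fallback grading scale for events outside CTCAE v3.0 (Protocol 6-2, item 8) mis-orders its top two labels and has no life-threatening level, although Grade IV is the trigger for stopping treatment and for emergency reporting

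*Protocol*

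**What the plan says.** **Grading.** Protocol 5-4-2 sets the main standard: "Adverse events are evaluated based on the Japanese-language Common Terminology Criteria for Adverse Events (CTCAE) v3.0". Section 6-2 item 8 repeats it and adds a fallback, to be applied on the attending physician's judgment: "adverse events not described by this standard are evaluated on a grade scale: I: mild, II: moderate, III: more severe, IV: severe".

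**Treatment.** Section 5-5-1 item 8 states: "If an adverse event of Grade IV occurs, the protocol treatment must be discontinued". Table 3 in 5-4-2 agrees, since Grade 4 stops protocol treatment at its first appearance. For Grade 3, Table 3 allows treatment to resume after the first onset (at dose reduction 1) and after the second (at dose reduction 2), and stops it at the third.

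**Reporting.** Section 9-1-2 lists this category for emergency reporting: "Unknown Grade 4 non-hematological toxicity". Section 9-1-3 adds life-threatening events, a term that "refers to known Grade IV hematological toxicities, known Grade 4 non-hematological toxicities", along with fever and bleeding symptoms. Under 9-2, "The study site supervisor will orally report to the study secretariat within 24 hours", and a written form follows within 72 hours.

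**The concern.** A grade in this protocol is more than a description. Grade IV alone ends protocol treatment and, for most kinds of event, starts a 24-hour reporting clock. A scale feeding those rules should place its top grade where the rules assume it to be. The fallback scale does not. It calls its top grade merely severe, calls the grade below more severe, and never mentions threat to life.

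At stake is how one patient is handled when an unlisted event is severe but not life-threatening. At Grade 3 the event can be managed with a pause and a lower dose. At Grade IV the patient loses the rest of the assigned 8 or 16 courses, and the site may owe an urgent report.

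**Working it through.** No figure in the plan needs reproducing. The check sets the provisions side by side. It treats Grade IV and Grade 4 as the same grade, since the protocol uses both numeral styles.

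**Step 1: order of the labels.** The fallback labels run mild, moderate, more severe, severe. In ordinary use the third is worse than the fourth, while the numerals say the reverse. A physician must either trust the numerals and ignore the words, or match the event to a word. The second route takes an event judged severe to Grade IV.

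**Step 2: meaning of the top grade.** Section 9-1-3 places known Grade IV/4 toxicities, hematological and non-hematological, in the life-threatening category. The fallback scale has no such level. The same grade number is therefore treated as life-threatening for reporting but described only as severe when it is assigned.

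**Step 3: treatment consequence.** Table 3 gives, for one event under each grade:

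| Recorded grade | 1st onset | 2nd onset | 3rd onset |
| --- | --- | --- | --- |
| 3 | Off-drug, resume at dose reduction 1 | Off-drug, resume at dose reduction 2 | Stop |
| 4 | Stop | not applicable | not applicable |

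Two Grade 3 onsets allow resumption and no Grade 4 onset does. The note to Table 3 counts all events of the same grade together, so the difference applies to a patient with at most one earlier Grade 3 onset. For a patient with two, a further Grade 3 event stops treatment anyway.

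**Step 4: reporting consequence.** Under 9-1-2, unknown means absent from the package insert or prescribing information. That is a different test from being absent from CTCAE v3.0, so an unlisted event can be known or unknown. If it is graded IV:

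| Type of toxicity | Known | Unknown |
| --- | --- | --- |
| Non-hematological | Reportable (9-1-3) | Reportable (9-1-2) |
| Hematological | Reportable (9-1-3) | Not reportable by grade under 9-1-2 or 9-1-3 |

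Three of the four cells need an oral report within 24 hours and a form within 72 hours. At Grade 3, neither 9-1-2 nor 9-1-3 requires a report on grade alone.

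**Step 5: any exemption.** Neither Table 3 nor 5-5-1 item 8 exempts grades given on the fallback scale. The allowance in 5-4-2 to continue at the same dose covers events such as alopecia or dysgeusia with no prospect of becoming serious. That does not plainly fit an event judged severe. Section 6-2 refers to an appendix for completing case record forms, which might anchor the grades, but it is not among the pages available.

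**The case against.** The strongest reply is that a clinician would read the scale sensibly. Four ascending steps make IV the worst, and III can be taken as more severe than moderate. A severe, non-life-threatening event then goes to III, and the text leaves that judgment to the physician. This stands in part. A reader might infer that the scale sends every severe unlisted event to Grade IV, and the documents do not support that. The labels are incoherent, so they permit that grade without forcing it.

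Second, the line may well be a translation slip. That is plausible and lowers its weight as evidence of a deliberate choice, but it is the printed rule and nothing else shown corrects it.

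Third, 9-1-3 is a reporting category and does not define how Grade IV is assigned. On that view a looser fallback scale is over-inclusive without being a formal contradiction. This is fair. The practical point remains, because the stop and the report depend on the grade number however it was reached.

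Fourth, 9-1-2 and 9-1-3 speak of toxicity, and only 9-1-1 says that causal relationship is irrelevant. Reporting of an unlisted Grade IV event judged unrelated to capecitabine is therefore arguable. The reporting consequence is stated here for toxicities only.

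Fifth, a reader might infer support from Table 5, where "Moist desquamation, ulcers, blisters, strong pain" with "Everyday activities are impossible" is Grade 3, and conclude that the fallback scale sits one grade higher. The documents do not support this either. Table 5 is limited to hand-foot syndrome by its own note, never uses the word severe, and has no Grade 4 level to compare with.

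Finally, any error is toward caution, the physician may stop treatment for an adverse event in any case (5-5-1 items 9 and 13), and capecitabine may be restarted after protocol termination (5-5-1 item 8). All of this is true and limits the harm, although a restart is outside protocol treatment.

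**Conclusion.** The point holds as a wording fault in an operative rule. The top two labels are not coherently ordered, and Grade IV has no life-threatening anchor where the stopping and reporting rules need one. A severe but non-life-threatening unlisted event could be graded IV, with the consequences traced above.

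The size is small. Only events outside CTCAE v3.0 are touched, and the protocol gives no frequency for them. A reader might infer a threat to the efficacy result. The documents do not support that: DFS events are recurrence, a new cancer lesion or death (7-1-1), and the primary analysis uses all enrolled subjects (8-2), so adverse event grade does not enter. Adverse events are tabulated by group without hypothesis testing (8-3 item 3).

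The conclusion assumes that Roman and Arabic grade numbers mean the same, and that the form-completion appendix does not already re-anchor the scale. If it does, 6-2 would still need to be brought into line with it.

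**What to change.** In 6-2 item 8, change the fallback scale to I: mild, II: moderate, III: severe, IV: life-threatening. Check the case report form instructions and align them if they carry the same wording. The cost is one line of the protocol and one check of the forms. Visits, data items, sample size and the analysis do not change.

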## **6-3. Checking Procedures for Recurrent and Non-Recurrent Cancerous Lesions**

As a general rule, subjects are examined every 3 months until postoperative day 3, and every 6 months from post-study year 3 onward for cancerous recurrence and appearance of tumor markers. In addition, imaging diagnoses are performed in the form of chest radiography or CT, and abdominal ultrasound examination or CT is performed every 6 months until postoperative year 5. When recurrence is suspected, recurrence is confirmed using appropriate imaging diagnoses such as colonoscopy and CT.

Imaging diagnostics for confirming recurrence include the following:

(1) Liver metastasis: ultrasonography or CT, magnetic resonance imaging (MRI)

(2) Lung metastasis: chest radiographic examination or CT

(3) Abdominal lymph node metastasis: ultrasonography or CT

(4) Local recurrence: CT, MRI, intestinal radiography, or endoscopy

The date of confirmation of recurrence and the confirmation method should also be included in the report submitted.

Document the presence/absence of nonrecurrent cancerous lesions, the site of detection (if applicable), and the date of confirmation in the report.

*M cancer is not treated as a cancerous lesion.

## **6-4. Outcome Investigation**

Outcome investigation (confirmation of survival) of enrolled subjects is conducted annually (every year). Remote outcomes such as survival may also be investigated following the end of the study period.

## **6-5. Discontinuation of Treatment Protocol**

1) Last day of drug administration

2) Date of decision to discontinue treatment

3) Reason for discontinuing treatment protocol

Table 6 Examination items and evaluation schedule

|  | Pre-enrollment | Postoperative Course (months) | | | | | | | | | | | |
| --- | --- | --- | --- | --- | --- | --- | --- | --- | --- | --- | --- | --- | --- |
|  | 1 year | | 2 years | | 3 years | | 4 years | |  | 5 years | |
| 3 6 9 12 | | 3 6 9 12 | | 3 6 9 12 | | 3 6 9 12 | | 3 6 9 12 | | | Months |
| Consent acquisition | ● |  | |  | |  | |  | |  | | |  |
| Patient background | ● |  | |  | |  | |  | |  | | |  |
| Disease assessment | ● |  | |  | |  | |  | |  | | |  |
| Pregnancy check (if necessary) | ● |  | |  | |  | |  | |  | | |  |
| Concomitant illnesses, treatments | ● |  | |  | |  | |  | |  | | |  |
| ECG | ● |  | |  | |  | |  | |  | | |  |
| Vital signs, PS | ● | In following with Table 7 | |  | |  | |  | |  | | |  |
| Hematological testing | ● |  | |  | |  | |  | | |  |
| Blood biochemistry testing | ● |  | |  | |  | |  | | |  |
| Adverse events and countermeasures |  |  | |  | |  | |  | | |  |
| Drug adherence |  |  | |  | |  | |  | | |  |
| Interviews/examinations |  | ● ● ● ● | | ● ● ● ● | | ● ● ● ● | | ● ● | | ● ● | | |  |
| CEA, CA 19-9 | ● | ● ● ● ● | | ● ● ● ● | | ● ● ● ● | | ● ● | | ● ● | | |  |
| Chest X-ray  CT | ● | ● ●  or or  ● ● | | ● ●  or  ● | | ● ●  or  ● | | ● ●  or  ● | | ● ●  or  ● | | |  |
| Abdom. ultrasound  CT | ●  or  ● | ● ●  or or  ● ● | | ●    ● | | ●    ● | | ●    ● | | ●    ● | | |  |
| Pelvic CT (colorectal cancer) |  | ●* ● | | ●* ● | | ● | | ● | | ● | | |  |
| Colonoscopy |  | ● | | ● | | ● | |  | |  | | |  |
| MRI* |  |  | |  | |  | |  | |  | | |  |

*: As necessary #: Search for cancerous recurrence at anastomosis site

Table 7-1 Group A: Standard-of-care group

|  | Postoperative Course (months) | | | | | | | | | | | | | | | | | |
| --- | --- | --- | --- | --- | --- | --- | --- | --- | --- | --- | --- | --- | --- | --- | --- | --- | --- | --- |
|  | 1 | |  | 3 | | |  | 6 | | |  | | 9 |  | | | | 12 |
| Dosing cycle | 1 | | 2 | 3 | 4 | 5 | 6 | 7 | 8 | - | - | - | - | - | - | - | - | |
| Weeks since treatment initiation | 1 | 2 | 4 | 7 | 10 | 13 | 16 | 19 | 22 | - | - | - | - | - | - | - | - | |
| PS |  | △ | ● | ● | ● | ● | ● | ● | ● |  | | | | | | | | |
| Hematological tests |  | △ | ● | ● | ● | ● | ● | ● | ● |  | | | | | | | | |
| Blood biochemistry tests |  | △ | ● | ● | ● | ● | ● | ● | ● |  | | | | | | | | |
| Adverse events and countermeasures | Subjects were monitored and data was recorded during the treatment period and for 28 days after completion of treatment | | | | | | | | |  | | | | | | | | |
| Drug adherence |  | | | | | | | | |  | | | | | | | | |

Table 7-2 Group B: Study treatment group

|  | Postoperative Course (months) | | | | | | | | | | | | | | | | | | |
| --- | --- | --- | --- | --- | --- | --- | --- | --- | --- | --- | --- | --- | --- | --- | --- | --- | --- | --- | --- |
|  | 1 | |  | 3 | | |  | 6 | | | | |  | 9 | | |  | | 12 |
| Dosing cycle | 1 | | 2 | 3 | 4 | 5 | 6 | | 7 | 8 | 9 | 10 | | 11 | 12 | 13 | 14 | 15 | 16 |
| Weeks since treatment initiation | 1 | 2 | 4 | 7 | 10 | 13 | 16 | | 19 | 22 | 25 | 28 | | 31 | 34 | 37 | 40 | 43 | 46 |
| PS |  | △ | ● | ● | ● | ● | ● | | ● | ● | ● | ● | | ● | ● | ● | ● | ● | ● |
| Hematological tests |  | △ | ● | ● | ● | ● | ● | | ● | ● | ● | ● | | ● | ● | ● | ● | ● | ● |
| Blood biochemistry tests |  | △ | ● | ● | ● | ● | ● | | ● | ● | ● | ● | | ● | ● | ● | ● | ● | ● |
| Adverse events and countermeasures | Subjects were monitored and data was recorded during the treatment period and for 28 days after completion of treatment | | | | | | | | | | | | | | | | | | |
| Drug adherence |  | | | | | | | | | | | | | | | | | | |

●: Necessary item　　△: Performed as necessary

# **7. Study Endpoints**

## **7-1. Primary Endpoint**

**7-1-1. Disease-free survival (DFS)**

1) Definition

The period from the enrollment date to the date of the first event confirmation.

2) Event definition

An event is defined as an instance of any of the following:

(1) Recurrence

(2) First occurrence of non-recurrent cancer lesions after the date of enrollment

(M cancer is not treated as a cancerous lesion)

(3) Death from any cause

Surviving subjects not deemed to exhibit cancerous lesions other than recurrences will be determined to have no cancerous lesions as of the final monitoring date.

3) Definition of relapse and recurrence date

Recurrence findings that fall under any of the following are defined as "recurrence". However, if possible, it is advisable to check recurrence via biopsy.

(1) Imaging diagnosis: Confirmation of recurrence based on imaging findings; the date diagnosis was determined is considered the recurrence date.

(2) Pathological diagnosis: If diagnosis of recurrence is made clinically prior to biopsy, the date of diagnosis is considered the recurrence date. If diagnosis could not be made and biopsy enabled diagnosis of recurrence, the biopsy date is considered the recurrence date.

(3) Clinical judgment: If recurrence cannot be confirmed by imaging diagnosis or pathological diagnosis because of rapid deterioration or transference, and clinical findings are reference only, the date of confirmation shall be the recurrence date. However, in such cases, the clinical findings that resulted in the judgment of recurrence should be recorded in the case report along with the confirmation date.

Recurrence does not include increases in tumor marker values.

